## Abstract

**Introduction:**

Chronic kidney disease (CKD) is a growing global public health concern, particularly in aging population. Despite the strong epidemiological evidence linking physical activity to improved kidney outcomes, interventional findings remain scarce and inconsistent. The primary purpose of the Aging Kidney and Exercise Training Study (AKETS) is to investigate whether a structured exercise program would attenuate the kidney function decline in middle–aged and older adults using a trial within cohorts (TwiCs) design.

**Methods:**

The AKETS is a 24–month, community–based, randomized controlled trial embedded in the prospective Aging Kidney Study cohort, which started in November 2018. A total of 141 participants aged 40–90 years are enrolled and allocated to one of the following three groups: (1) exercise intervention, (2) stretching intervention (active control), and (3) usual lifestyle (time control). The exercise program comprises individualized multicomponent training, including aerobic, resistance, and balance exercises, performed three times per week over 12 months.

**Results:**

The primary outcome is the slope of the estimated glomerular filtration rate (eGFR) based on serum cystatin C. The secondary outcomes include renal hemodynamics, mineral metabolism, cardiovascular function, body composition, muscle strength, and physical performance. At baseline, the exercise, stretching, and usual lifestyle groups were well matched for key demographic and clinical characteristics, such as age, proportion of women, and eGFR.

**Conclusion:**

Findings from the AKETS will allow for a robust evaluation of exercise as a primary preventive strategy for CKD and are expected to inform future nonpharmacological interventions targeting kidney health in the aging population.

**Trial registration:**

This study is registered at the University Hospital Medical Information Network Clinical Trials Registry as UMIN000055825. Registered on the 13th of October 2024.

**Supplementary Information:**

The online version contains supplementary material available at 10.1186/s12882-025-04471-y.

## Introduction

Chronic kidney disease (CKD), defined by persistent abnormality of kidney structure and/or function, is a major global public health concern [1, 2]. The prevalence of CKD is expected to increase rapidly as the average age of the world’s population continues to rise [3]. In fact, in Japan, which has entered an ultra–aged society, approximately 15 million people (or one in seven adults) have developed CKD [4]. CKD often develops without noticeable symptoms [5], leading to multiple adverse outcomes, including cardiovascular events and renal replacement therapy (dialysis or kidney transplantation), cognitive and physical decline, hospitalization, and all–cause mortality [6, 7]. Although advances in pharmacotherapy [8, 9] —such as renin–angiotensin system inhibitors and sodium–glucose cotransporter 2 inhibitors— have improved control of established risk factors (i.e., hypertension and diabetes), the CKD population continues to increase. This highlights the persistent lack of effective non–pharmacological strategies to slow kidney function decline, particularly among middle–aged and older adults.

Structural and functional changes in the kidneys that occur as part of the aging process constitute a fundamental pathophysiological basis for CKD and are crucial factors for determining the subsequent severity of CKD progression [10, 11]. Moreover, renal hemodynamic alterations [12] and disturbed mineral metabolism [13] observed from early midlife may contribute to the pathogenesis of CKD. Therefore, suppressing or delaying these changes may effectively mitigate CKD progression in later life. Notably, a decline in the glomerular filtration rate beyond physiological tolerance limits (i.e., rapid kidney function decline), facilitated by deterioration in renal hemodynamics and mineral metabolism, is closely linked to long–term renal outcomes, making it a primary target for preventive interventions.

Several cross–sectional studies have reported that individuals with higher levels of physical activity and performance tend to have better kidney function [14–18]. Furthermore, longitudinal studies have demonstrated an independent association of physical activity and fitness with preventing CKD development and rapid kidney function decline [19–23]. Recent evidence from animal model studies also indicates the potential renoprotective effects of long–term exercise training in various CKD models [24–28]. These epidemiological and basic findings suggest that exercise training aimed at improving physical activity and fitness could be an effective strategy for preventing CKD development [29, 30]. However, it remains possible that declines in kidney function may lead to reduced muscle mass and impaired physical performance, subsequently resulting in lower physical activity levels (i.e., reverse causation). Indeed, evidence in humans from the limited number of randomized controlled trials (RCTs) investigating whether exercise training benefits kidney health has been inconsistent [31–34]. Therefore, the renoprotective effects of exercise training remain uncertain and controversial, highlighting the need for rigorously designed interventional studies to clarify causality.

The inconsistent findings from exercise–nephrology RCTs may stem from the possibility that kidney aging is irreversible and progresses slowly with significant individual variations. Thus, when investigating the effects of exercise training on kidney health, within–group (intra–individual) comparisons may be more critical than between–group (inter–individual) comparisons. To achieve both comparisons, the trial within cohorts (TwiCs) study design, in which the intervention study is performed within a prospective observational cohort with regular measurements [35, 36], is considered more appropriate than conventional standard RCTs. The TwiCs study design allows for an evaluation of not only within–group changes and between–group differences but also the long–term effects of exercise training intervention, because regular measurements in the prospective cohort will be continued after the completion of the intervention period [37].

By using the TwiCs study design, the current study involving middle–aged and older adults aims to investigate whether a 1–year progressive moderate– to high–intensity exercise training program can slow kidney function decline and renal hemodynamics/mineral metabolism deteriorations. The hypotheses for this study are as follows: (1) 1–year of structured exercise training will attenuate the kidney function decline while improving renal hemodynamics and mineral metabolic status. Specifically, we hypothesize that the annualized rate of kidney function decline during the 1–year intervention period will be smaller than the annualized rate observed during the 5–year pre–intervention observational period within the same individuals assigned to the exercise group. (2) Additionally, we hypothesize that increases in physical activity and fitness levels will be positively associated with favorable changes in kidney function. To our knowledge, this study is the first to apply the TwiCs study design in the field of sports nephrology. The current study is expected to provide new insights regarding the effectiveness of nonpharmaceutical interventions for CKD development.

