### Sample size calculation

The sample size calculation for this clinical trial is based on a previous study that explored the impact of a 1–year structured rehabilitation program on kidney function decline among patients with CKD, using a small sample from a TwiCs study design [49]. According to this previous study, the annual slope of eGFR (mL/min/1.73 m²/year) was approximately + 2 in the intervention group and − 3 in the control group, indicating a between–group difference of approximately 5 units per year. Assuming a standard deviation of 8, a two–sided significance level of 0.05, and a statistical power of 0.80, a total of 84 participants would be required based on a two–sample t–test.

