### Statistical analysis

All analyses will be conducted based on the intention–to–treat (ITT) principle. Statistical significance is set at *P* < 0.05. Data are expressed as mean ± standard deviations, median [interquartile range], or frequency counts (%), as appreciate. Baseline group characteristics will be compared using one–way analysis of variance or the Kruskal–Wallis test for continuous variables and the chi–square test or Fisher’s exact test for categorical variables. The eGFR slope for the 6–year pre–intervention, 1–year during–intervention, and 1–year post–intervention phases will be calculated. For calculating the eGFR slope, the repeated measurements of eGFR will be analyzed using a linear mixed model (LMM) including continuous time as a fixed effect and individual participant as a random effect (henceforth, Model 1). In addition, the slope will be estimated using a single linear regression of eGFR on time by each participant (called as Model 2) as a supplementary analysis.

For a primary analysis, the eGFR slope will be compared using the LMM including the group (exercise, stretching, and usual lifestyle), time, their interaction term, and the baseline eGFR as fixed effects and individual participant as a random effect. The eGFR slopes calculated by Models 1 and 2 will also be compared between groups using analysis of covariance, including the group as a factor and the eGFR slope of the 6–year pre–intervention phase as a covariate. The eGFR slope for the 6–year pre–intervention, 1–year during–intervention, and 1–year post–intervention phases will be performed using paired t–tests for within–group comparison.

Secondary outcomes will be analyzed using the generalized estimating equations (GEE) method, including group, categorical time point (baseline, 6 months, and 1 year), and their interaction term as factors. In each model, an unstructured (UN) correlation matrix will be used to account for within–individual correlations across time points. If the UN matrix leads to a convergence problem for numerical optimization, a simpler correlation structure will be used. The results of the GEE analysis will be presented as the marginal means with 95% confidence intervals. Pearson product–moment correlation analysis and repeated–measure correlation analysis [50] will be conducted to examine the associations between individual changes in each outcome.

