A key difference between the handful of previous interventional studies examining the effects of exercise training on kidney health in individuals with or without CKD and our study is the fact that our study has the long–term observational data spanning six years before intervention initiation. This difference is important for addressing the clinical question of whether exercise can improve deteriorating kidney health, which has worsened over several years owing to aging and long–term lifestyle disruptions. To our knowledge, only one pilot study has been conducted with a similar design comparing changes in kidney function before and after the intervention, suggesting that exercise training can slow the progressive deterioration in kidney function in patients with CKD [49]. However, this pilot study had a small sample size (*n* = 20) and short pre–intervention follow–up period (one year) and did not conduct follow–up measurements after the intervention. Therefore, we aimed to address these limitations by adopting a better design (i.e., TwiCs) to clarify whether exercise improves, does not affect, or deteriorates kidney health.

Emerging evidence suggests that the deterioration in renal hemodynamics [12] and mineral metabolism [13] observed in early middle age may contribute to the rapid kidney function decline in later life. Based on these findings, preventive measures to minimize the deterioration of renal hemodynamics and mineral metabolism may lead to improved long–term renal outcomes. However, the long–term effects of preventive interventions on renal hemodynamics and mineral metabolism remain unclear. In this study, as a secondary outcome, we comprehensively investigated the effects of long–term structured exercise training on renal hemodynamics and mineral metabolism in middle–aged and older adults. This will allow us to provide new insights into the underlying mechanisms through which exercise training contributes to the suppression of kidney function decline.

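### Specific hypothesis 1 is an uncontrolled before-after comparison within the exercise arm, whereas the sample size and primary model are between groups, and no exercise-versus-stretching contrast over 0-12 months is named as primary

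*Protocol article*

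**What the plan says.** All references are to the protocol article.

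- **Introduction, hypotheses.** The specific form of hypothesis 1 is that the exercise group's annual decline over the intervention year "will be smaller than the annualized rate observed during the 5–year pre–intervention observational period within the same individuals assigned to the exercise group". Stretching does not appear in it. The preceding rationale says that "within–group (intra–individual) comparisons may be more critical than between–group (inter–individual) comparisons".
- **Statistical analysis, within group.** Slopes are defined for a pre-intervention, a during-intervention and a post-intervention phase. The comparison of these "phases will be performed using paired t–tests for within–group comparison".
- **Statistical analysis, primary.** "For a primary analysis, the eGFR slope will be compared using the LMM including the group (exercise, stretching, and usual lifestyle), time, their interaction term", with baseline eGFR as a further fixed effect and participant as random effect. No time window is given for this model.
- **Statistical analysis, additional.** "The eGFR slopes calculated by Models 1 and 2 will also be compared between groups using analysis of covariance", with the 6-year pre-intervention slope as covariate.
- **Sample size calculation.** A between-group difference of about 5 per year, SD 8, two-sided 0.05 and power 0.80, from which "a total of 84 participants would be required based on a two–sample t–test".
- **Randomization and blinding.** Only exercise and stretching are randomised (1:1). The usual lifestyle group is chosen by preference.
- **Discussion.** "our study has the long–term observational data spanning six years before intervention initiation", against five years in hypothesis 1.

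**The concern.** Hypothesis, sample size and primary model should answer one question, and here they do not. The specific hypothesis asks whether the exercise arm did better than its own past. The sample size and the primary model ask whether groups differ.

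The first question cannot isolate exercise. Anything that moves eGFR slopes between the cohort years and the trial year (assay drift, season of sampling, a change of habits on joining a trial) counts as an exercise effect. The stretching arm exists to remove such influences, but the hypothesis as worded does not use it. Read literally, it could be called confirmed without the randomised comparison. The limitations in the Discussion do not mention this risk.

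The between-group side is also loosely fixed. The group factor has three levels, one of them self-selected, and the randomised contrast is not singled out. Three phases are defined, yet the primary model has one linear time term and no window, so the phase to which its group-by-time term refers is open.

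**Working it through.** **1. The plan's own figure.** Inputs (Sample size calculation): difference 5, SD 8, two-sided 0.05, power 0.80. Standardised difference = 5/8 = 0.625. The exact two-sample t calculation gives 41.17, so 42 per arm and 84 in total, with power 0.808. The figure reproduces as a comparison of two groups. With the 43 and 45 participants in Table 1, power is 0.826.

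**2. The within-arm test under no exercise effect.** Suppose slopes shift by d per year in every arm for reasons unrelated to exercise. The paired test in the exercise arm (n = 43, 42 degrees of freedom, critical value 2.018) has noncentrality d × √43 / SD. The article gives no SD for a paired slope difference. SD 8 is borrowed from the sample size section, and 6 and 10 show the range. The shifts are also assumptions.

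| Common shift d (mL/min/1.73 m² per year) | Noncentrality, SD 8 | P(significant), SD 8 | SD 6 | SD 10 |
|---|---|---|---|---|
| 1 | 0.82 | 13% | 19% | 10% |
| 2 | 1.64 | 36% | 57% | 25% |
| 3 | 2.46 | 67% | 89% | 49% |

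The nominal rate is 5%. A difference between the two randomised arms is unaffected, because d cancels.

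**3. What the planned ANCOVA tests.** Let D be the during-phase slope, P the pre-intervention slope and G the group. The ANCOVA is D = a + bG + cP + e. Subtracting P from both sides gives D − P = a + bG + (c − 1)P + e. The coefficient b is the same, so this is a between-group test of change in slope, given the earlier slope. It falls short in three ways:

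- it is additional to the primary model, which adjusts for baseline eGFR and not for the earlier slope;
- its group factor includes the preference-based group;
- no exercise-minus-stretching contrast is named.

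There is also a practical point. The outcome section describes the slope model as having random intercepts. Model 1 in that form gives no participant-specific slopes, so the ANCOVA and the paired tests can run as written only on Model 2, the separate regressions that the plan calls supplementary.

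**4. The time window.** Take a true effect of 5 per year gained over year 1 and then retained, so that the group difference is 0, 2.5, 5 and 5 at 0, 0.5, 1 and 2 years. Fit one straight line by ordinary least squares:

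- 0-12 months (three visits): Sxy/Sxx = 2.5/0.5 = 5.0 per year.
- 0-24 months (four visits, mean time 0.875): Sxy/Sxx = 5.3125/2.1875 = 2.43 per year.
- 0-24 months with the effect gone by month 24: −0.3125/2.1875 = −0.14 per year.

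Holding SD at 8 for simplicity, 43 versus 45 gives power 0.83 for a difference of 5 and about 0.29 for 2.43. The stated effect and power therefore belong to the 0-12 month window.

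**5. The pre-intervention period.** Hypothesis 1 gives five years. Statistical analysis and Discussion give six. This period defines the comparator in hypothesis 1 and the covariate in the ANCOVA.

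**The case against.** The strongest reply is that the between-group comparison is already primary. The sample size matches a two-group comparison exactly, the mixed model is named as primary, and the paired tests are not. The Introduction says the design was chosen to allow both kinds of comparison, and hypothesis 1 opens with a general statement about attenuating decline that the primary model can address. All of that stands, and it limits the point to a mismatch between the specific hypothesis and the rest of the plan.

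Three stronger readings are tempting, and the article does not support them.

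- A reader might infer that no test compares the change in slope between the randomised arms. The planned ANCOVA does so in substance (step 3). The fault is its rank and the undefined contrast.
- A reader might infer that six years of pre-intervention values enter the primary model as outcomes and dilute the effect to a small fraction. That is an unlikely reading of a model that adjusts for baseline eGFR. The window question is between 0-12 and 0-24 months.
- A reader might infer that a significant result in exercise and a non-significant one in stretching will be offered as proof. Nothing in the text says so.

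It is also fair that an article may leave the time window to a fuller document. Here, however, the article defines three phases and sizes the trial on an annual effect, so the phase of its primary test decides whether the stated power applies.

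**Conclusion.** The point holds in this form: the specific hypothesis is an uncontrolled within-arm contrast, while the sample size and primary model are between groups, and the randomised 0-12 month contrast is never named as primary. The probability of a misleading within-arm result is about 13% to 67% for common shifts of 1 to 3 per year at SD 8. Those figures depend on assumed shifts and a borrowed SD; the lack of a control does not. The fall from 5 to about 2.4 per year assumes a 0-24 month window and an effect retained after year 1; over 0-12 months there is no dilution. The difference between five and six years is a plain contradiction. The changes are specific and cheap, and they should be made before outcome data are analysed.

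**What to change.** 1. Restate hypothesis 1 as the exercise-minus-stretching difference in eGFR slope over 0-12 months.
2. Name that contrast and window as the primary analysis, adjusted for the pre-intervention slope. Either make the planned ANCOVA primary or add the pre-intervention slope to the mixed model. If the ANCOVA is chosen, say which participant-level slopes it uses, since a random-intercept model supplies none. A full three-phase model with random slopes is not required.
3. Report comparisons with the usual lifestyle group as non-randomised and secondary.
4. Label the within-group paired t-tests descriptive.
5. Give one length for the pre-intervention period throughout.

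The cost is wording, modest analysis work and a downgraded within-arm claim. The sample size need not rise on this account. For the ANCOVA the residual SD is 8 × √(1 − r²), where r is the correlation between earlier and during-phase slopes. Assuming r from 0 to 0.4, it runs from 8 to 7.33, which needs 42 down to 35 per arm before dropout.

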## Methods

### Study design, procedure, and ethics

The Aging Kidney and Exercise Training Study (AKETS) is a 24–month, community–based, two–arm RCT using the TwiCs study design (Fig. 1) and is conducted within the Aging Kidney Study (AKS) cohort, which started in November 2018 with the aim of investigating the associations between age–related changes in mineral metabolism and kidney health in individuals with and without CKD (UMIN000034741). The AKS cohort is a uniquely comprehensive dataset encompassing physiological, biochemical, behavioral, and physical performance measures relevant to kidney health, enabling multifactorial analyses of potential risk and protective factors associated with age–related kidney function decline. Cross–sectional analyses from the AKS cohort have already identified some novel lifestyle factors of kidney health [38–43], highlighting the potential importance of non–pharmacological strategies to slow kidney function decline. Such preliminary evidence from the AKS cohort provides a strong rationale for conducting the current study. The AKETS protocol includes four assessment time points: baseline, 6 months (midpoint), 12 months (end of intervention), and 24 months (follow–up) (Fig. 1).

**Fig. 1 Fig1:**
[figure not shown]
Study overview. The Aging Kidney and Exercise Training Study (AKETS) is a 24–month, community–based, two–arm RCT that employs the trial within cohorts (TwiCs) study design. The AKETS protocol includes four assessment time points: baseline, 6 months (midpoint), 12 months (end of intervention), and 24 months (follow–up)

Ethical approval was granted by the Institutional Review Board of the University of Tsukuba (approval no. 2029) in accordance with the guidelines of the Declaration of Helsinki and Belmont Report. Written informed consent has been obtained from all participants before participating in the study. This study is registered at the University Hospital Medical Information Network Clinical Trials Registry as UMIN000055825 and is funded by the Japan Agency for Medical Research and Development, Core Research for Evolutional Science and Technology, Cross–Ministerial Strategic Innovation Promotion Program, and Japan Society for the Promotion of Science.

